### Analyses

Clinic-level outcomes will be evaluated using descriptive statistics (recruitment and feasibility) and qualitatively (key informant interviews). Participant-level outcomes will also be evaluated using descriptive statistics, both overall and stratified by participant type (parents vs adolescents), nicotine product used (cigarettes with or without vaping vs vaping only), and clinic where recruitment occurred. Recruitment outcomes will be compared by participant gender. Given that this is a pilot trial with insufficient power to formally test the effectiveness of CEASE, exploratory analyses comparing smoking and vaping cessation, use of cessation resources, and motivation to quit smoking and vaping between intervention and control participants will be performed to identify potential trends and signals of effectiveness in all 4 participant groups.

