**Figure 1 figure1:**
[figure not shown]
Study flow diagram illustrating participant trajectory through study of a brief digital screening and intervention tool for parental and adolescent tobacco and electronic cigarette use. CEASE: Clinical Effort Against Secondhand Smoke Exposure.

The recruitment target is 100 individuals who report using tobacco or e-cigarettes (either tobacco or e-cigarettes alone, or both tobacco and e-cigarettes) in the 7 days before responding to the study questionnaire. A minimum of 50 parents and 50 adolescents will be recruited.

The study will be reported according to the Strengthening the Reporting of Observational Studies in Epidemiology Statement: Guidelines for Reporting Observational Studies [26].

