#### Control Condition

The control condition is care as is usually delivered in participating clinics. Current practice at those sites does not currently include routine provision of assistance for parental nor adolescent smoking and e-cigarette cessation (eg, referral to quit lines and NRT prescription). Participants in the control conditions will complete the same questionnaire as those in the intervention group; however, they will not be presented with a list of resources at the end of the questionnaire. While completing the final 6-month follow-up questionnaire, participants in the control group will be offered the option to receive a 1-time direct linkage to CEASE smoking and vaping cessation resources (behavioral supports and NRT recommendation).

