### Allocation

This study aims to recruit an equal number of parent and adolescent users. Parent and adolescent participants are randomized to the intervention and control groups using a 1:1 ratio. Parent and adolescent participants are stratified into 2 subgroups: those who smoke traditional combustible cigarettes (with or without e-cigarette use) and those who report exclusive use of e-cigarettes. A computer-generated randomization list created by a biostatistician external to the study team is used to randomize participants within each group.

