**Protocol fidelity**								
	Baseline questionnaire completion	Proportion of participants who complete the baseline questionnaire out of randomized participants (REDCap^a^ survey)	✓				Baseline questionnaire	≥90%
	Access to web-based resources	Proportion of participants who want to be connected to the web-based resources who report access these resources (self-report)	✓	✓	✓	✓	Baseline and follow-up questionnaires	N/A^b^
	Access to quit lines (phone, or SMS text messaging support)	Proportion of interested participants who received a communication from the quit lines (self-report)		✓	✓	✓	Baseline and follow-up questionnaires	N/A
	Access to NRT^c^	Proportion of participants who want to receive NRT who receive a report receiving a formal written recommendation or prescription for NRT	✓	✓	✓	✓	Baseline and follow-up questionnaires	N/A
	NRT use	Proportion of participants who have used NRT (self-report)		✓	✓	✓	Baseline and follow-up questionnaires	N/A

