**Study retention**								
	Participant retention	Proportion of randomized participants that could be contacted (initiation of REDCap survey, phone, or email contact) at follow-up		✓	✓	✓	Follow-up questionnaires	≥80%
	Smoking and vaping status	Availability of self-reported smoking and vaping status for randomized participants		✓	✓	✓	Follow-up questionnaires	≥80%
	Completion of data at follow-up	Complete survey data available for randomized participants		✓	✓	✓	Follow-up questionnaires	≥60%
	Cotinine testing	Availability of cotinine testing results		✓	✓	✓	Web-based portal	N/A

^a^REDCap: Research Electronic Data Capture.

^b^N/A: not applicable.

^c^NRT: nicotine replacement therapy.

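### Retention and data completeness have no planned summary by randomised arm, the resource-access and NRT fidelity rows are not limited to the intervention arm, and an observational reporting guideline is named for a randomised pilot

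*Protocol article*

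**What the plan says.** **Summaries.** The Analyses section of the protocol article describes participant-level outcomes overall and "stratified by participant type (parents vs adolescents), nicotine product used (cigarettes with or without vaping vs vaping only), and clinic where recruitment occurred". It then plans exploratory comparisons of cessation, "use of cessation resources, and motivation to quit smoking and vaping between intervention and control participants will be performed". Those are the only analyses by arm that it names.

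**Retention rows of Table 2.** Contact at follow-up is the "Proportion of randomized participants that could be contacted", with a threshold of at least 80%. The next row is "Availability of self-reported smoking and vaping status for randomized participants", also at least 80%. Complete survey data has a threshold of at least 60%, and cotinine availability has none. No threshold is specific to an arm.

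**Fidelity rows of Table 2.** Access to quit lines is the "Proportion of interested participants who received a communication from the quit lines (self-report"). Access to web resources and to an NRT recommendation is likewise taken among participants who want them. NRT use is taken among participants, with no condition. None of these four rows names an arm, and none carries a feasibility threshold.

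**Control arm.** Under Control Condition, controls fill in the same questionnaire, but "they will not be presented with a list of resources at the end of the questionnaire". They are offered the resources at the 6-month questionnaire.

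**Design and reporting.** Under Allocation, "Parent and adolescent participants are randomized to the intervention and control groups using a 1:1 ratio". Under Study Design, Setting, and Participants, "The study will be reported according to the Strengthening the Reporting of Observational Studies in Epidemiology Statement".

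**The concern.** The listed strata go down to the recruiting clinic but leave out the one factor that the trial randomises. Two readings suffer.

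*Retention.* Participants and research assistants are unblinded, and research assistants make the reminder calls. Intervention participants can obtain resources at each time point, whereas controls wait until the end. Dropout could therefore differ between arms, in either direction. A pilot meant to inform a fully powered trial needs to show whether it does, and a pooled proportion cannot.

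*Fidelity.* A control who wants NRT and has no recommendation at month 1 or 3 shows the protocol working, but would count against fidelity. A control who finds the resources independently is the contamination that the article lists among its limitations, but would count as fidelity achieved. If controls are in the denominator, the proportion measures neither delivery nor contamination.

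The reporting guideline is a separate, smaller mismatch: an observational checklist is not built around allocation and participant flow by arm.

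**Working it through.** **1. The plan's own retention figure.** Power Calculations gives 44.2% to 75.8% as the 95% CI for 60% completion with 50 participants in an age group, both arms together. The usual formula gives 0.60 ± 1.96 × √(0.60 × 0.40 / 50) = 0.60 ± 0.136, or 46.4% to 73.6%. The stated interval is not reproduced. That is a separate matter and nothing below depends on it. What matters here is that the plan's retention precision is stated by age group only, not by arm.

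**2. Which Table 2 rows have an arm comparison.**

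| Table 2 row | Denominator as written | Arm comparison in Analyses |
|---|---|---|
| Baseline questionnaire completion | randomised | none; applies equally to both arms, so no dilution |
| Web resources, quit lines, NRT recommendation | those interested, arm not stated | partly, through use of cessation resources |
| NRT use | participants, arm not stated | yes, as use of cessation resources |
| Contact, status available, complete data | randomised, both arms | none |
| Cotinine results available | not stated | none |

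**3. Pooled retention.** With 1:1 allocation, pooled = (arm 1 + arm 2) / 2. The arm rates are assumptions:

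- (70% + 90%) / 2 = 80%
- (72% + 88%) / 2 = 80%
- (60% + 100%) / 2 = 80%

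All three give the threshold value, with gaps of 20, 16 and 40 points.

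**4. Fidelity.** If a share w of a row's denominator belongs to the intervention arm, pooled = w × (intervention rate) + (1 − w) × (control rate).

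- For NRT use the denominator is all participants, so w is about 0.5. An assumed intervention rate of 80% with control rates of 0%, 10% or 20% pools to 40%, 45% or 50%.
- For the rows conditional on interest, w is unknown. With assumed rates of 80% and 10%: w = 0.5 gives 45%; w = 0.75 gives 0.75 × 80 + 0.25 × 10 = 62.5%; w = 1 gives 80%, with no dilution.

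**5. Precision of a by-arm report at the planned size**, taking 80% retention in both arms.

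- One arm, overall (50 per arm): 1.96 × √(0.8 × 0.2 / 50) = ±11.1 points.
- One arm within an age group (25 per arm): 1.96 × √(0.8 × 0.2 / 25) = ±15.7 points.
- Difference overall: 1.96 × √(2 × 0.16 / 50) = ±15.7 points.
- Difference within an age group: 1.96 × √(2 × 0.16 / 25) = ±22.2 points.

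At assumed rates of 70% and 90% the half-width of the difference is 1.96 × √(0.21/50 + 0.09/50) = 15.2 points overall, and 1.96 × √(0.21/25 + 0.09/25) = 21.5 points within an age group. The second exceeds the 20-point gap itself.

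**The case against.** The case on the other side has real weight.

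- A reader might infer that fidelity is never looked at by arm. The article does not support that: use of cessation resources is to be compared between intervention and control participants in all four groups, which overlaps the access and NRT-use rows. The comparison is framed as a search for signals of effectiveness, however. It does not change how the Table 2 proportions are defined, and it does not touch retention.
- A reader might infer that controls are certainly in the interest-based denominators. The text is ambiguous. The question about interest in behavioural support or NRT sits in the Assess step of the intervention, which would keep controls out. The control description says they complete the same questionnaire, which would bring them in. Dilution is possible on the wording but not established.
- A reader might infer that differential attrition is concealed. The article only leaves it off its list. The recruitment log records randomisation and retention, so the counts exist. The flow diagram is not visible here, and a condensed article may leave by-arm attrition tables to a fuller plan. What stands is that the article does set out a list of strata and a list of arm comparisons, and retention by arm is in neither.
- A reader might treat a 20-point retention gap as detectable. With 50 per arm the standard error is 7.7 points (15.2 / 1.96), so power is only about 73%. Within an age group the interval is wider than the gap.
- A reader might take STROBE as the reason why arm is missing. A reporting checklist does not set analysis strata, and the article does plan arm comparisons. The mismatch stands by itself.

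The four resource rows carry no threshold, and the primary outcome is the recruitment rate, so neither is affected by any of this.

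**Conclusion.** The point holds in a limited form. Followed as written, the plan gives a retention figure that can meet 80% with a large gap between arms, and access and NRT proportions that may combine delivery in one arm with contamination in the other. It also names an observational guideline for a trial that the article itself calls a pilot randomised controlled trial.

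The size cannot be fixed from the article. The 70%/90% retention split and all the resource-use rates above are illustrations. Dilution ranges from none, if only intervention participants are asked about interest, to about half the weight of each proportion, if both arms contribute equally. Baseline questionnaire completion and the recruitment outcomes are not affected.

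This is a worthwhile correction that costs almost nothing. It does not threaten the feasibility conclusion on recruitment, and it should not be read as saying that the trial could formally test for differential attrition.

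**What to change.** 1. In Analyses, add randomised arm to the strata for the Table 2 outcomes.
2. Report contact, status availability, complete data and cotinine availability by arm, with the difference and its 95% CI. State that these are descriptive, with half-widths of about 15 to 16 points overall and 22 points within an age group at the planned size.
3. In Table 2, define the web-resource, quit-line, NRT-recommendation and NRT-use rows among intervention participants (interested ones where the row is conditional on interest). Show the same quantities in controls, labelled as contamination. State whether controls are asked about interest. If they are not, give the control figures over all controls.
4. Replace STROBE with the CONSORT extension for randomised pilot and feasibility trials, with participant flow by arm.

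The cost is wording in the analysis section and Table 2, plus one column per table. No new data are needed, because the log already holds randomisation and retention. Blinded analysis can be kept by tabulating under coded arms and attaching the labels at the end.

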### Ethical Considerations

This study was reviewed and approved by the Institutional Review Board of the Sainte-Justine University Hospital Research Centre (2023-4237) and has been registered on ClinicalTrials.gov (NCT05366790). Any modifications or deviations from the protocol or adverse events will be recorded in the study logs on REDCap and reported immediately (within 48 hours) to the Institutional Review Board of the Sainte-Justine University Hospital Research Centre.

## Results

This study obtained funding in April 2022. Research activities for this study began in June 2022. Participant enrollment and data collection began in February 2023 and are expected to be completed in 9 months (October 2023). As of September 30, 2023, a total of 115 participants—61 parents and 54 adolescents—have been recruited and have completed all baseline data. Data analysis will begin once all participants have been recruited and follow-up measures (1, 3, and 6-month follow-up) are in progress. The primary results of this study are expected to be available in the first months of 2025.

## Discussion

### Potential

This is the first study to test the feasibility and preliminary effectiveness of the CEASE intervention in Canada, as well as with adolescents and individuals with exclusive e-cigarette use. If shown feasible by reaching the feasibility recruitment threshold of 6 parent and 6 adolescent participants per month, this study could allow for the planning of a full-scale randomized controlled trial testing CEASE’s effectiveness in Canada in these populations.

### Strengths and Limitations

This study includes several strengths. First, it builds on the CEASE intervention, which has previously been demonstrated to be effective and cost-effective. Second, the electronic format of the screening and intervention will facilitate the integration of the tool in clinic workflow without any required intervention from clinical staff and will help with scale-up to additional sites. Finally, the study leverages existing cigarette and e-cigarette cessation resources, foregoing the need for additional costs for resource development. This also means that those resources can evolve and improve over time without affecting the design or feasibility of the study.

This study has certain limitations. Given the pilot nature of the study and the small sample size, this study does not have the statistical power to evaluate the effectiveness of the CEASE intervention. This study is also being conducted exclusively in an urban tertiary care hospital, which may not be reflective of pediatric clinics in community hospitals or other primary care clinics. Nonetheless, as recruitment is taking place in both general pediatric and adolescent medicine clinics as well as several specialized pediatric clinics, it allows for testing of the CEASE model in a diverse parent and adolescent patient group. Given this diversity of participants and recruitment clinics within a single center, we elected to randomize at the participant level rather than following the cluster-randomization protocol previously used to evaluate CEASE [23]. This decision does, however, pose a risk of contamination, wherein participants in the control group learn of the intervention and choose to seek out these publicly available smoking cessation resources themselves. While this may result in a decreased effect size of “The Clinical Effort Against Secondhand Smoke Exposure–Canada” (CanCEASE) in this study, all participants are offered access to these resources at the end of the study period, and the CanCEASE questionnaire itself may prompt individuals wishing to quit smoking or vaping to seek out these publicly available resources themselves during the study. Furthermore, cluster randomization would have been impractical in the context of this pilot study, as a larger sample size is required.

Logical next steps for our work will be to consider expanding CEASE recruitment to other clinic settings, including primary and secondary care clinics as well as rural settings, and conducting a full-scale cluster randomized controlled trial.

### Conclusions

Cigarette smoking and nicotine vaping remain highly prevalent among parents and adolescents. Pediatric clinics represent an underutilized opportunity for the promotion of healthy lifestyle behaviors. This study tests the feasibility and preliminary effectiveness of a simple approach to smoking and vaping cessation. If successful, it could pave the way for a large-scale randomized controlled trial testing the effectiveness of this approach for adolescents and parents who smoke and vape in a Canadian setting. It also has the potential to inform clinicians and researchers about preferred cessation tools for parents and adolescents who use cigarettes and e-cigarettes, which remains an understudied area.

It is anticipated, based on previous implementation of CEASE in the United States, that CEASE will be feasible, as determined by a satisfactory recruitment rate as well as high proportions of participants interested in cessation, referral to cessation services, and NRT. As such, the data obtained through this study will help inform the design and implementation of a fully powered randomized controlled trial of CEASE in Canada.

## Appendix

Multimedia Appendix 1 Consent form (English) for participation in a randomized-controlled pilot trial evaluating the feasibility and preliminary effectiveness in Canadian pediatric clinics of a brief digital screening and intervention tool for parental and adolescent tobacco and electronic cigarette use.

Multimedia Appendix 2 Key informant interviews.

Multimedia Appendix 3 Peer Review Reports from the Canadian Institutes of Health Research (CIHR).

## Abbreviations

CanCEASE: The Clinical Effort Against Secondhand Smoke Exposure–Canada
CCS: Canadian Cancer Society
CEASE: Clinical Effort Against Secondhand Smoke Exposure
CQTS: Conseil Québécois sur le Tabac et la Santé
NRT: nicotine replacement therapy
REDCap: Research Electronic Data Capture
